According to current guidelines, a relatively low starting dose is prescribed and repeated measurements of plasma levels of drug and active metabolite (Therapeutic Drug Monitoring, TDM) are necessary to guide and individualize the dose of TCA. Unfortunately, large inter-individual differences exist in the relationship between TCA dose and plasma levels. For patients with *increased* activity of specific cytochrome P450 (CYP) isoenzymes (Ultrarapid Metabolizers, UM) dosing as usual is inefficient as initial TCA concentrations tend to be low and it takes several weeks to reach the therapeutic window. The subsequent delay is associated with enduring personal suffering, increased numbers of hospital days, increased risk for suicidal behaviour and eventually lower recovery rates for depression. Patients with *decreased* CYP450 activity (Intermediate Metabolizers (IM) and Poor Metabolizers (PM)) have relatively high systemic exposure to TCAs. Traditional dose finding may be accompanied by the occurrence of increased rates of adverse effects. These adverse effects

are inconvenient (dry mouth, sedation) but may also be dangerous (confusion, respiratory depression and cardiac arrhythmia).

Inter-individual differences in activity of CYP450 isoenzymes are determined by genetic variants (polymorphisms) in the associated *CYP* genes. The Pharmacogenetics Working Group of the Royal Dutch Association for the Advancement of Pharmacy (KNMP) and the international Clinical Pharmacogenetics Implementation Consortium (CPIC) published dosing strategies for TCAs based on genetic variants in *CYP2D6* and *CYP2C19* ([name] et al. 2011; <https://kennisbank.knmp.nl>; Hicks et al. 2016). To this end, randomized trials focussing on effectiveness, prevention of adverse effects and cost-effectiveness of genotype based dosing in larger groups of patients are not available from the literature (Hicks et al. 2016).

Therefore, the added value of pharmacogenetics is still unknown. Information on (cost)effectiveness is essential before further implementation can be decided on and genotype based dosing can be included in psychiatric prescription guidelines.

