## 6.3 Study procedures

The table below shows the procedures according to the research proposal.

|                             | Visit
day
week                                                                           | 1
-7
-1 | 2
0 | 3
7
1 | 4
14
2 | 5
21
3 | 6
28
4 | 7
35
5 | 8
42
6 | 9
49
7 |
|-----------------------------|------------------------------------------------------------------------------------------------|---------------|--------|-------------|--------------|--------------|--------------|--------------|--------------|--------------|
| Procedure            |                                                                                                |               |        |             |              |              |              |              |              |              |
| Informed consent            | x                                                                                              |               |        |             |              |              |              |              |              |              |
| SCID-I                      | x                                                                                              |               |        |             |              |              |              |              |              |              |
| Psychiatric assessments     | x                                                                                              |               |        |             |              |              |              |              |              |              |
| Medical history             | x                                                                                              |               |        |             |              |              |              |              |              |              |
| CYP 450 genotype            | x                                                                                              |               |        |             |              |              |              |              |              |              |
| Laboratories + ECG          | x                                                                                              |               |        |             |              |              |              |              |              |              |

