**Description:**

To maximize generalization of the results we aim to perform the study according to the principles of high standard care for severely depressed patients for whom a tricyclic antidepressant is prescribed. Therefore the baseline investigations include a formal psychiatric assessment which includes SCID-I (Structured Clinical Interview for DSM-IV Axis I: a clinical interview designed to elicit the DSM-IV criteria). Based on the SCID-I we conclude if patients fulfil psychiatric inclusion criteria. Other routine procedures in clinical practice are assessments of Medical history, physical examination and Laboratory investigations (Hb, Ht, Ery's, Leuco's, Diff, Na, K, Ureum, Creat, ASAT, ALAT, LDH, yGTP, Free T4, TSH) and ECG (only when indicated), examination physical examination are all in agreement with the procedures that should be offered in high standard clinical care and cannot considered to be a extra burden to the patients. Based on these investigations we can decide if patients fulfil inclusion criteria.

Repeated administration of scales for the measurements of the depressive symptoms (HAM-D/QIDS), adverse events (ASEC and FIBSER) and the measurements of TCA plasma levels are also in agreement with careful common clinical practice.

To answer the main research question, CYP450 genotyping will take place (blood withdrawal will take place together with that for laboratory investigations). At baseline and after 7 weeks we will take plasma for storage and the SRRS-6 retardation scale (Widlöcher et al. 1989; observational scale scored by the researcher), will be administrated. Twelve hours after the first TCA dose an early plasma TCA level will be measured. Other interventions are administration of the assessment instruments for cost effectivity analysis (see below).

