### **7.5 [Data Safety Monitoring Board (DSMB) / Safety Committee]**

We do not expect that patients in this study are exposed to extra risks besides the risks of venepuncture. Instead we expect lower risk levels (see Summary section, paragraph on Burden and Risks, and see the following paragraph 11 on Structured risk analysis). A DSMB is not needed in this study.

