## 11. STRUCTURED RISK ANALYSIS

Potential issues of concern. The only extra risk participants are exposed to is the risk associated with the extra venepunctures. The aim of the study is to decrease the risk associated with CYP450 unadjusted prescription of TCA's. In the intervention group we therefore expect lower chances for side effects and a reduced time to therapeutic response compared to treatment as usual. The weekly monitoring for side effects and depressive symptoms in all participating patients give a low burden to the patients but contribute to extra safety compared to regular care.

Because the only risk is determined by the venepunctures the items below are not applicable.

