**The following section is not applicable.**

- a. Level of knowledge about mechanism of action
- b. Previous exposure of human beings with the test product(s) and/or products with a similar biological mechanism
- c. Can the primary or secondary mechanism be induced in animals and/or in *ex-vivo* human cell material?
- d. Selectivity of the mechanism to target tissue in animals and/or human beings
- e. Analysis of potential effect
- f. Pharmacokinetic considerations
- g. Study population
- h. Interaction with other products
- i. Predictability of effect

i. Can effects be managed?

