## APPENDIX B.

De bepaling van de metabolisatiefenotypen op basis van de uitslagen van het genetisch onderzoek zal gebeuren volgens de richtlijnen

Algemene achtergrondtekst Farmacogenetica - CYP2D6

Algemene achtergrondtekst Farmacogenetica - CYP2C19

Welke zijn te vinden op [www.kennisbank.knmp.nl](http://www.kennisbank.knmp.nl)

APPENDIX C. Pharmacogenetics based dose advice (KNMP see [www.kennisbank.knmp.nl](http://www.kennisbank.knmp.nl)).

| Gene               | CYP2D6                          |             |                                |                                | CYP2C19     |             |             |                                |
|--------------------|---------------------------------|-------------|--------------------------------|--------------------------------|-------------|-------------|-------------|--------------------------------|
| Metaboliser status | UM                              | EM          | IM                             | PM                             | UM          | EM          | IM          | PM                             |
| Clomipramine       | increase dose to 150% of normal | normal dose | decrease dose to 70% of normal | decrease dose to 50% of normal | -           | -           | -           | -                              |
| Imipramine         | increase dose to 170% of normal | normal dose | decrease dose to 70% of normal | decrease dose to 30% of normal | normal dose | normal dose | normal dose | decrease dose to 70% of normal |
| Nortriptyline      | increase dose to 160% of normal | normal dose | decrease dose to 60% of normal | decrease dose to 40% of normal | -           | -           | -           | -                              |

In this study we primarily follow KNMP guidelines, as these guidelines do not contain dosing guidance for patients with both *CYP2D6* and *CYP2C19* deviant metabolizer status we follow table 4 from Hicks et al. (2016). This table of Hicks et al. (2016) assumes additive effects in patients with double deviant metabolizer status. Clinical pharmacogenetics implementation consortium guideline (CPIC) for CYP2D6 and CYP2C19 genotypes and dosing of tricyclic antidepressants: Clin Pharmacol Ther. 2016 Dec 20. doi: 10.1002/cpt.597.

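### Section 11 calls venepuncture the only extra risk although randomisation sets the initial dose (150–170% of normal in CYP2D6 ultrarapid metabolisers, down to 30% in poor metabolisers), and the visit 1 ECG is stated two ways

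*Protocol*

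**What the plan says.** **Risk.** Protocol section 11 says "The only extra risk participants are exposed to is the risk associated with the extra venepunctures", and section 11.1 repeats the point. Section 11 then draws a consequence: "Because the only risk is determined by the venepunctures the items below are not applicable". The items set aside include "Pharmacokinetic considerations", interactions, and whether effects can be managed. Section 7.5 refers to section 11 and to the burden-and-risk paragraph of the Summary, and concludes: "A DSMB is not needed in this study". The Summary and section 7.5 are worded more softly than section 11. They give an expectation that no risk is added beyond blood sampling, and that risk will on balance fall.

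**Dosing.** Under section 3, Strategy 1, the initial dose follows the pharmacogenetic guideline set out in Appendix C. For a CYP2D6 UM on imipramine the entry is "increase dose to 170% of normal"; for nortriptyline it is 160% and for clomipramine 150%. PM entries are 50% (clomipramine), 40% (nortriptyline) and 30% (imipramine). Under Strategy 2 the dose rises over the first week to the standard dose.

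**Known dangers.** Section 1 says that adverse effects of high tricyclic exposure "may also be dangerous (confusion, respiratory depression and cardiac arrhythmia"). It also says that the added value of pharmacogenetics is not yet known.

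**ECG.** The visit table in section 6.3 has a row "Laboratories + ECG", marked at visit 1 with no condition. The description under the table says "ECG (only when indicated").

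**The concern.** The dose is part of what is randomised. A statement that blood sampling is the only added risk is therefore wrong on the protocol's own terms, whatever the net balance turns out to be. Lower risk in the intervention arm is one of the hypotheses under test, so it cannot also be the reason for declaring that dose-related risk is absent. The statement has consequences: section 11 uses it to set its risk items aside, and section 7.5 leans on section 11 for the DSMB decision.

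The ECG entries leave sites and monitors with two readings of one screening procedure. The section 6.3 description says that these investigations help decide eligibility, and exclusion criterion 9 concerns medical contraindications to tricyclics such as recent infarction.

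On the analysis side, the intervention raises the dose in UM and lowers it in intermediate metabolisers (IM) and PM. Opposite effects on exposure can offset each other in an overall comparison of arms. The subgroup comparison that section 8.2 fixes is deviant against normal metabolisers, which is not a randomised contrast. The effect of the changed dose is seen by comparing arms within phenotype.

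**Working it through.** The plan gives no figure for this risk, so there is none to reproduce. The check sets the statements side by side and adds one illustration.

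**1. Does allocation change the drug dose?** Yes. Section 3 ties the initial dose in Strategy 1 to Appendix C and the initial dose in Strategy 2 to the standard guideline. For a CYP2D6 UM, IM or PM the two arms therefore aim at different doses before any steady-state level is known. Levels are measured 7 days after the last dose change. A 12-hour level is also taken, but the objectives name it only as a predictor and no dose action on it is stated.

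**2. Which patients, and in which direction?** From Appendix C, CYP2D6 entries, as a percentage of normal:

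| Drug | UM | IM | PM |
|---|---|---|---|
| Clomipramine | 150 | 70 | 50 |
| Nortriptyline | 160 | 60 | 40 |
| Imipramine | 170 | 70 | 30 |

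The 150–170% range applies to CYP2D6 UM only. A CYP2C19 UM has the normal dose for imipramine and no entry for the other two drugs.

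**3. What if the phenotype does not predict clearance?** Inputs are the therapeutic ranges in section 6.1.1, the Appendix C factors, and the linear kinetics assumed by the dosing algorithm in section 3. Assume a patient who is classified UM, has normal clearance, and would sit at the middle of the range on the normal dose. Then level = midpoint × UM factor.

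| Drug | Range (mg/l) | Midpoint × factor | Level | Above upper limit |
|---|---|---|---|---|
| Clomipramine | 0.20–0.30 | 0.25 × 1.5 | 0.375 | 0.375/0.30 = 1.25, so 25% |
| Imipramine | 0.15–0.30 | 0.225 × 1.7 | 0.383 | 0.3825/0.30 = 1.275, so 28% |
| Nortriptyline | 0.05–0.15 | 0.10 × 1.6 | 0.16 | 0.16/0.15 = 1.07, so 7% |

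The same assumption for a patient wrongly classified PM gives levels below range: 0.25 × 0.5 = 0.125 (lower limit 0.20), 0.225 × 0.3 = 0.068 (0.15) and 0.10 × 0.4 = 0.04 (0.05) mg/l, in the same drug order. Section 1 links delay in reaching the therapeutic window to suicidal behaviour, so under-exposure is not a venepuncture risk either.

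**4. ECG.** The table entry is unconditional, the description is conditional, and the visit 1 narrative that follows does not mention an ECG. The texts do not settle which one governs.

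**The case against.** The strongest reply is that the net risk probably falls. The drugs are registered, the dosing guidelines are published and already used in selected centres, and the raised dose is meant to offset faster metabolism. If the Appendix C factors restore a mid-range level, a PM given the normal dose in the control arm would reach 0.25/0.5 = 0.50 (clomipramine), 0.225/0.3 = 0.75 (imipramine) or 0.10/0.4 = 0.25 mg/l (nortriptyline). Those excesses are larger than the UM illustration and need no misclassification. Weekly ratings, level monitoring, withdrawal for intolerable reactions, SAE reporting and an exclusion for interacting drugs are all in place. This stands as support for an expectation of lower risk. It does not support the word only.

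Several stronger readings are tempting, and the documents do not carry them:

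- **A DSMB is needed.** A reader might infer this. The documents show only that part of the stated ground for doing without one is wrong. The need itself is for the sponsor and ethics committee to judge, as is whether to complete the risk template.
- **5–10% of UM calls are false.** Sections 3 and 6.3 say that the tested variants explain 90–95% of cases with changed enzyme activity. The remainder are mainly altered metabolisers in whom no variant is found, who would be dosed as normal. No rate of false UM calls is given.
- **Patients are misinformed.** The patient information is not available, so this cannot be checked.
- **Imipramine patients deviant for both genes receive extrapolated doses.** Section 6.2 switches them to nortriptyline.
- **Patients on 170% go without cardiac screening.** Nothing in the protocol links the ECG to the dose factor, and history and physical examination are done at visit 1. The description could also be read as qualifying the table row. The discrepancy is then minor, but it still has to be resolved.
- **Harm in UM would be hidden.** Phenotype is a randomisation stratum, so the comparison by arm can be made, and an analysis plan may already contain it.

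**Conclusion.** The point holds as an internal contradiction. Sections 11 and 11.1 cannot stand beside section 3, Appendix C and section 1: randomisation alters the initial dose in both directions, and the protocol itself names the dangers of high exposure. The two ECG statements in section 6.3 conflict and need reconciling.

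The size is that of the dose change: 150–170% of normal in CYP2D6 UM, and down to 30% in PM. The excesses of 25%, 28% and 7% over the upper limit rest on three assumptions: normal clearance in a patient classified UM, a mid-range level on the normal dose, and linear kinetics. They show that exposure depends on a correct prediction; they do not estimate how often it fails. UM prevalence is not given either, and the protocol does not say whether the adjusted dose is built up during the first week. No sample size, significance level or power changes. The correction should be made because it is specific, cheap and concerns patient safety.

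**What to change.** 1. **ECG.** Reconcile the visit table and the description in section 6.3 so that all sites follow one rule at visit 1. Which rule is for the sponsor and ethics committee to decide.
2. **Risk statements.** Correct sections 11 and 11.1 to say that randomisation changes the initial dose: raised in CYP2D6 UM, lowered in IM and PM. Keep the lower net risk in the Summary and section 7.5 as an expectation. Restate the DSMB decision on that corrected premise, without presuming its outcome.
3. **Safety table.** From data already collected, tabulate by arm within phenotype: first steady-state levels above range, side effects, withdrawals for adverse reactions, and SAEs. If an analysis plan already provides this, a cross-reference is enough.

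The cost is an amendment to the protocol wording and one additional table. The phenotype groups will probably be small, so the table can describe but not test. If the sponsor settles on the table's version of the ECG, the added procedure is one that the schedule already lists.

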**The following section is not applicable.**

- a. Level of knowledge about mechanism of action
- b. Previous exposure of human beings with the test product(s) and/or products with a similar biological mechanism
- c. Can the primary or secondary mechanism be induced in animals and/or in *ex-vivo* human cell material?
- d. Selectivity of the mechanism to target tissue in animals and/or human beings
- e. Analysis of potential effect
- f. Pharmacokinetic considerations
- g. Study population
- h. Interaction with other products
- i. Predictability of effect

i. Can effects be managed?

### 11.1 Synthesis

As already explained the only risk consists of the extra vene punctures.

## APPENDIX A. VARIANTS FOR GENOTYPING

| Genotype      | Variation                                               | RS number                                                                    | Gene location | Assay ID       |
|---------------|---------------------------------------------------------|------------------------------------------------------------------------------|---------------|----------------|
| CYP2C19 *2    | 681 G>A                                                 | RS4244285                                                                    | Exon 5        | C__25986767_70 |
| CYP2C19 *3    | 636 G>A                                                 | RS4986893                                                                    | Exon 4        | C__27861809_10 |
| CYP2C19 *17   | -806 C>T                                                | RS12248560                                                                   | 5'-UTR        | C__469857_10   |
| CYP2D6*1 (WT) |                                                         |                                                                              |               |                |
| CYP2D6*2      | 2850C>T,
4180G>C                                     |                                                                              |               |                |
| CYP2D6 *3     | 2549 delA                                               | RS35742686                                                                   | Exon 5        | C__32407232_50 |
| CYP2D6 *4     | 1846 G>A                                                | RS3892097                                                                    | Exon 4        | C__27102431_B0 |
| CYP2D6 *5     | Gene deletion                                           |                                                                              | All exons     | Hs00010001_cn  |
| CYP2D6 *6     | 1707 delT                                               | RS5030655                                                                    | Exon 3        | C__32407243_20 |
| CYP2D6*7      | 2935A>C                                                 | rs5030867                                                                    |               |                |
| CYP2D6*8      | 1758G>T                                                 | rs5030865                                                                    | Intron        |                |
| CYP2D6*9      | 2615-2617delAAG                                         | rs5030656                                                                    |               |                |
| CYP2D6*10     | 100C>T                                                  | rs1065852                                                                    |               |                |
| CYP2D6*15     | 137insT                                                 |                                                                              |               |                |
| CYP2D6*17     | 1023C>T                                                 | rs28371706                                                                   |               |                |
| CYP2D6*29     | 1659G>A;
1661G>C;
2850C>T;
3183G>A;
4180G>C | rs61736512(T)
rs1058164(C)
rs16947(A)
rs59421388(T)
rs1135840(C) |               |                |
| CYP2D6*35     |                                                         |                                                                              |               |                |
| CYP2D6*41     | 2988 G>A                                                | RS28371725                                                                   | Intron 6      | C__34816116_20 |
| CYP2D6 xn     | Gene duplication                                        |                                                                              | All exons     | Hs00010001_cn  |

